#### 9.5.4 Analysis of time to first confirmed 6-month persistent cervical HPV infections

|                                                           | Covariates                                       | Type    | Categories                                               | Time-dependent | Comment                      |
|-----------------------------------------------------------|--------------------------------------------------|---------|----------------------------------------------------------|----------------|------------------------------|
| Demographic characteristics
(defined at subject level) | Region                                           | Class   | Europe
Asia Pacific
Latin America
North America | No             |                              |
| Behavioral Covariates
(defined at subject level)       | Smoking                                          | Ordinal | [0-0.5[ pack/year
≥0.5 pack/year                      | No             |                              |
|                                                           | Age at beginning of sexual activity (years)      | Ordinal | Never had sexual intercourse
<15
15-17
18-25    | No             |                              |
|                                                           | Number sexual partner during the previous year   | Ordinal | 0
1
2-3
≥4                                      | No             |                              |
|                                                           | Marital status                                   | Binary  | Living or lived with a partner
Single                 | No             | Re-assessed at yearly visits |
|                                                           | At least one previous pregnancy                  | Binary  | No
Yes                                                | No             | Re-assessed at each visit    |
|                                                           | Hormones for contraception or another indication | Binary  | No
Yes                                                | No             | Re-assessed at each visit    |
|                                                           | Intra-uterine device                             | Binary  | No
Yes                                                | No             | Re-assessed at each visit    |
|                                                           | Sterilized                                       | Binary  | No
Yes                                                | No             | Re-assessed at each visit    |
|                                                           | Chlamydia trachomatis                     | Binary  | No
Yes                                                | No             | Re-assessed at each visit    |

|                     | Covariates                      | Type | Categories                                                                   | Time-dependent | Comment            |
|---------------------|----------------------------------------|-------------|-------------------------------------------------------------------------------------|-----------------------|---------------------------|
| Clinical covariates | Previous cervical HPV infection | Class       | No
Yes, with at least one high risk HPV type
Yes, with only low risk HPV type | No                    | Re-assessed at each visit |

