## 4.4 Determinant definitions

### 4.4.1 Reference cervical HPV infections used for definitions

The definitions of some determinants as well as their potential inclusion in the different statistical analyses will be based (when relevant) on the cervical HPV infections referenced in the analyzed endpoint:

- For a **histopathologically-confirmed CIN2+ (or CIN1+, or CIN3+) associated with the same HPV type as a previous confirmed 6-month persistent cervical HPV infection**, the reference cervical HPV infection will be the 6-month persistent infection,
- For a **histopathologically-confirmed CIN2+ (or CIN1+, or CIN3+) associated with the same HPV type as a previous cervical HPV infection (any cervical HPV infection)** the reference cervical HPV infection will be the cervical HPV infection,
- For the **clearance of a cervical HPV infection**, the reference cervical HPV infection will be the cervical HPV infection for which the clearance is observed,
- For a **first detected incident cervical HPV infection (or a first confirmed 6-month persistent cervical HPV infection)** following the start of sexual activity, the reference cervical HPV infection will be the first cervical HPV infection (or first confirmed 6-month persistent cervical HPV infection).

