Consequently any cervical HPV infection which onset is prior to the onset of the reference cervical HPV infection will be considered as a previous cervical HPV infection and any cervical infection which onset if after the end of the reference cervical HPV infection and before the occurrence of the event will not be considered as a co-infection.

However, when analyzed as time-varying covariables, co-infections will be considered until the occurrence of the event (e.g., lesion).

The following determinants will be defined for the purpose of analyzing immunosubset but they won't be included as covariates in the multivariable models:

- Serology status (based on ELISA) at study entry (Month 0) for HPV-16: Negative; Positive.
- Serology status (based on ELISA) at study entry (Month 0) for HPV-18: Negative; Positive.

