### **6.2.7 Analysis of time to first detected cervical HPV infections**

#### **6.2.7.1 Population**

The population for the analysis of time between the start of sexual activity and a first detected incident cervical HPV infection (or a first confirmed 6-month cervical HPV infection) will be restricted to subjects from the TVC-1-Control arm cohort for whom the date of start of sexual activity is known (i.e. either collected or computed, so that a starting date is available for the computation of the time between the start of sexual activity and a first detected cervical HPV infection) and for whom the date of start of sexual activity is either less than 6 months prior to their inclusion in the study or during the follow-up period.

Subjects with cervical HPV infections preceding the start of sexual activity will not be taken into account in the analyses.

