#### **6.2.7.2 Analysis unit**

The statistical unit for this analysis will be the subject.

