### 6.2.7.4 Time computation

The time to a first detected incident cervical HPV infection (or a first confirmed 6-month cervical HPV infection) following the start of sexual activity will be calculated in days as: Date of event or Date of censoring - Date of start of sexual activity.

The date of start of sexual activity will be determined as follows:

- For subjects who already had sexual intercourse prior to study entry: the date of start of sexual activity will correspond to the birthdate collected in the CRF plus the age at first sexual intercourse collected in the baseline behavioral questionnaire,.
- For subjects who did not have sexual intercourse prior to study entry: the date of start of sexual activity will correspond to the maximum between i) the date of the yearly questionnaire in which subjects reported having first sexual intercourse (or the date of the visit corresponding to the yearly questionnaire if the date of the questionnaire is missing) and ii) the date of the preceding detected cervical HPV infection, minus the date of the preceding questionnaire (or visit), divided by 2. In case there is no preceding questionnaire (i.e. baseline questionnaire is missing and first sexual intercourse is reported in the 1-year questionnaire), the date of start of sexual activity will be equal to the date of the 1-year questionnaire (or visit) minus 6 months.

The date of event will be:

- the date of the detection of the first incident cervical HPV infection (or the date of onset or the first confirmed 6-month cervical HPV infection) during the 48-month follow-up period,

The date of censoring will be:

- the date of Month 48 visit for cervical HPV infections of subjects who attended all visits during the 48-month follow-up period and did not have any cervical HPV infection during this period,
- the date of the last PCR reported at the latest visit for which data are available or the date of the last cytology (if the date is after the date of the last PCR) for cervical HPV infections of subjects who did not attend all visits during the 48-month follow-up period and who did not have any cervical HPV infection throughout their follow-up period (from first to last visit).

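### In the time-to-first-persistent-infection model, previous HPV infection is listed as not time-dependent although every Yes arises after time zero, so its hazard ratio is biased, in a direction the SAP leaves open

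*SAP*

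**What the plan says.** - **Clock.** SAP 6.2.7.4 measures time as "Date of event or Date of censoring - Date of start of sexual activity".
- **Population.** SAP 6.2.7.1 takes women whose debut was "either less than 6 months prior to their inclusion in the study or during the follow-up period", and adds: "Subjects with cervical HPV infections preceding the start of sexual activity will not be taken into account in the analyses".
- **Unit.** SAP 6.2.7.2: "The statistical unit for this analysis will be the subject".
- **Reference infection.** For this endpoint, SAP 4.4.1 states that "the reference cervical HPV infection will be the first cervical HPV infection (or first confirmed 6-month persistent cervical HPV infection"), so the reference infection is the event.
- **Meaning of previous.** SAP 4.4.2 says that any infection whose "onset is prior to the onset of the reference cervical HPV infection will be considered as a previous cervical HPV infection".
- **Covariate entry.** The 9.5.4 table lists "Previous cervical HPV infection" (No; Yes with a high-risk type; Yes with low-risk types only). The time-dependent column says No and the comment is "Re-assessed at each visit".
- **Who stays in.** In the 6.2.7.3 examples, subject B has two transient infections and is included with a persistent event of 0. In annex 9.4.3, subjects #3 and #5 have transient infections only and are said not to enter the first-persistent analysis.
- **Which determinants.** SAP 6.2.7.5 limits the determinants to those that start before the first detected infection.

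**The concern.** A covariate fixed at one value per woman must be known at time zero. Here it cannot be, because a woman becomes Yes only by acquiring an infection after debut while still free of persistent infection. The fixed value therefore encodes part of the outcome history (immortal-time bias).

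The entry seems to have been carried over from 9.5.1. There it is sound: in the lesion models the reference infection starts the clock, so earlier infections are known at time zero. In 9.5.4 the reference infection ends the clock.

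At stake is the only clinical covariate in the 9.5.4 table, in a model that serves a named secondary objective. Its hazard ratio would be read as the effect of an earlier infection on the risk of a persistent one. A larger sample does not reduce the error.

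**Working it through.** The SAP gives no hazard ratio, event count or infection rate for this model, so there is no figure to reproduce.

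**Step 1: can any fixed coding work?**
- Frozen at debut: No for all women, so no hazard ratio can be estimated.
- Scored up to event or censoring: Yes depends on how long the woman stayed event-free.
- Scored relative to the reference infection, as 4.4.1 and 4.4.2 say: undefined for women without a persistent infection, for whom the SAP gives no rule.

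**Step 2: does the re-assessment comment rescue it?** SAP 6.2.4.5, which 6.2.7.5 adopts, treats re-assessed covariates as a time-independent class, apart from time-dependent ones. In 9.5.1, co-infection carries the same comment but has Yes in the time-dependent column. The column, not the comment, makes the distinction.

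**Step 3: size with all women kept (subject B reading).** Assumed: 48-month probabilities of transient / persistent infection as in the table, true hazard ratio 1, independent infection times, 6-monthly detection, follow-up 18 to 54 months, four runs of 20,000 women per setting. Let *e* be the share with the event, *q* the share coded Yes, and *r* the share coded Yes among women with the event. Risk in Yes women = *e·r/q*. Risk in No women = *e(1−r)/(1−q)*.

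| Transient / persistent | e | q | r | Risk, Yes | Risk, No | Fixed HR | Time-dependent HR |
|---|---|---|---|---|---|---|---|
| 0.30 / 0.15 | 0.11 | 0.20 | 0.10 | 0.11×0.10/0.20 = 0.055 | 0.11×0.90/0.80 = 0.124 | 0.37 | 0.99 |
| 0.50 / 0.30 | 0.22 | 0.32 | 0.18 | 0.22×0.18/0.32 = 0.124 | 0.22×0.82/0.68 = 0.265 | 0.35 | 1.01 |
| 0.60 / 0.20 | 0.14 | 0.42 | 0.22 | 0.14×0.22/0.42 = 0.073 | 0.14×0.78/0.58 = 0.188 | 0.32 | 0.98 |

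Further simulations, including nine settings with non-persistent infection hazards of 0.01 to 0.03 and persistent infection hazards of 0.005 to 0.015 per month, widen the fixed range to about 0.25 to 0.43. The time-dependent range becomes 0.93 to 1.06.

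**Step 4: size with transient-only women left out (annex 9.4.3 reading).** Every remaining Yes woman is then a case, so the risk among Yes women is 1 by construction, against 0.124 to 0.265 among No women in the table. The fixed hazard ratio under no effect becomes 1.6 to 6.3 in one set of runs and 1.4 to 5.6 in another.

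**Step 5: a true effect, all women kept, independent times.**

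| True HR | Fixed | Time-dependent |
|---|---|---|
| 1.5 | 0.46–0.56 | 1.44–1.49 |
| 2 | 0.59–0.73 | 1.85–1.96 |
| 3 | 0.80–1.03 | 2.60–2.83 |

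**Step 6: shared susceptibility (gamma frailty), all women kept, true HR 1.** With variance 0.5, fixed gives 0.52–0.57 and time-dependent 1.47–1.55. With variance 1.0, fixed gives 0.74–0.80 and time-dependent 2.17–2.24. Across all scenarios the fixed value is about 2.6 to 3.3 times lower than the time-dependent one.

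**The case against.** The best defence is that the re-assessment comment, together with 6.2.4.5, which speaks of updating behavioural determinants over follow-up and allows a counting-process approach, leaves room to program an updated value. A subject-level unit does not forbid several intervals per woman. If it were programmed that way, the timing bias would disappear. This stands as a possible reading, but it contradicts the table's own entry and so still needs a correction.

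Four stronger readings are tempting, and the SAP does not support them:

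- **The hazard ratio is falsely protective.** That follows only if transient-only women stay in as non-cases. Subject B says they do and annex 9.4.3 says they do not, which reverses the bias.
- **A harmful effect would always be hidden or reversed.** Even with all women kept, a strong association can remain above 1. In one frailty scenario the fixed value is 1.41 where time-dependent coding gives 3.85: attenuated, but visible.
- **Non-cases would be dropped as missing under 4.5.2.** That rule concerns determinants from the questionnaire or CRF. Previous infection is derived from PCR, and the SAP gives no rule for its value in non-cases.
- **Estimates for the other determinants are distorted.** This is plausible in an adjusted model, but no calculation here shows it.

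It is also fair that this is one covariate in the last-listed secondary objective, reported in a stand-alone report.

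**Conclusion.** The entry in 9.5.4 is wrong as written. A fixed value cannot be known at time zero, and its hazard ratio is biased under no effect whichever way 6.2.7.3 and 9.4.3 are reconciled: about 0.25 to 0.43 if transient-only women are kept, and about 1.4 to 6.3 if they are left out. No direction can be claimed until that contradiction is settled.

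That a fixed value is invalid follows from the SAP's definitions alone. The sizes rest on assumed infection rates, independent infection times and simplified 6-monthly detection. With shared susceptibility the fixed value moves closer to 1, but it stays far below the time-dependent estimate when all women are kept. Time-dependent coding removes the timing error. It does not remove confounding by shared susceptibility, so the corrected hazard ratio should be read as an association.

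The primary CIN2+ analysis is not affected.

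**What to change.** 1. In 9.5.4, set the time-dependent column to Yes for this covariate. Code No from sexual debut until the visit at which another infection is first detected, then Yes (high risk, or low risk only) from that visit. Use counting-process intervals for all women, which also gives non-cases a defined value.
2. In annex 9.4.3, correct subjects #3 and #5 so that women with only non-persistent infections stay in the first-persistent analysis as censored, in line with subject B in 6.2.7.3.
3. In 6.2.7.5, state that for this endpoint the determinants are those that start before the first persistent infection. Read literally, the present wording bars the covariate that 9.5.4 lists.

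The cost is one table entry, two text edits and some programming. SAP 6.2.4.5 already names the counting process as an option, though for repeated observations per subject and not specifically for this purpose. No new data are needed.
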